#### Data Analysis

To assess changes in pharmacists’ and technicians’ task and time distribution after implementation, we will calculate the proportion of total observed time in each task category by study period (before vs after implementation) for each pharmacy. The proportions of total observed time where pharmacists complete tasks with technicians or alone and use different information tools will also be calculated for each pharmacy. To assess the extent to which the introduction of MedSafeMap increased opportunities for pharmacists and technicians to engage with patients in CCM, we will examine changes in the time pharmacists and technicians spent in (1) having discussions with each other on responding to opportunities (ie, identifying patients with complex chronic health conditions who would benefit from CCM) and attending to unexpected threats (ie, personnel absences) and (2) having discussions with patients about medications [60]. *Z* tests for proportions will be used to compare the extent of before and after implementation change in the proportion of total observed time for each task category in each pharmacy site. A significance level of *P*<.05 will be used as well as the Holm approach to account for multiple comparisons, with 95% CIs based on the large sample normal approximation.

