#### Data Collection

Observations will be purposely scheduled across a variety of weekday shifts to maximize data variability and capture the full pharmacy workday. One observer will shadow a pharmacist equipped with a tablet with the WOMBAT software installed on it, while, at the same time, a similarly equipped second observer will shadow a technician. In total, 2 pharmacists and 2 technicians will be observed at each pharmacy. Observations will be limited to three 2-hour sessions per day, each separated by a brief break to reduce participant or observer fatigue. During each break, observers will note down any thoughts regarding future questions or more in-depth observation. The pharmacists and technicians will be observed for 36 hours both before and after implementation, over a 72-hour period. We estimate observing tasks across 72 hours in each pharmacy [55], yielding 432 hours across the 6 participating pharmacies [57,60].

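### If the simultaneous pharmacist and technician records are pooled, the Z test counts a conversation between the two shadowed staff twice and understates the variance of the staff-discussion outcome

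*Protocol article*

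**What the plan says.** The protocol article, Methods, Aim 3, Data Collection, has one observer follow a pharmacist, "while, at the same time, a similarly equipped second observer will shadow a technician". Staffing and volume are given in the same section: "In total, 2 pharmacists and 2 technicians will be observed at each pharmacy"; "Observations will be limited to three 2-hour sessions per day"; "The pharmacists and technicians will be observed for 36 hours both before and after implementation, over a 72-hour period". The planned total is 72 hours per pharmacy and 432 hours over the six sites.

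The Aim 3 Data Analysis section names two outcomes for whether MedSafeMap gave staff more opportunity to engage patients in CCM. One is the time pharmacists and technicians spend "having discussions with each other on responding to opportunities" and attending to unexpected threats. Z tests for proportions are to "compare the extent of before and after implementation change in the proportion of total observed time for each task category in each pharmacy site", at 5% with the Holm method and 95% intervals from the normal approximation. The strata named are task category, period and pharmacy. Role is not among them, although a separate proportion for pharmacists alone is also planned (tasks done together with a technician or unaccompanied). Nothing is said about matching the two records or allowing for their dependence.

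**The concern.** For most tasks, two observers following two people record two different things. For a conversation between the two people being followed, they record one event, and each tablet holds a copy. If both records go into one proportion, the numerator contains that event twice and the denominator contains the same clock time twice. The ratio is unharmed, but the Z test treats the copies as separate observations.

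This outcome is one of two used to judge whether the intervention worked as intended. The intervention may also act on exactly these events: the list of potential MedSafeMap components includes a pharmacist-technician huddle. An interval that is too narrow here would make an ordinary fluctuation between the two periods look like an effect at a site.

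**Working it through.** **Inputs from the document:** two simultaneous observers, one per role; at most three 2-hour sessions a day; 36 hours per period; six pharmacies; 5% level. Sidedness is not stated, so two-sided is taken.

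**Input not in the document:** f, the share of recorded discussion time that is between the two people shadowed at that moment. It is shown over its range.

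**1. The plan's hours.** (36 + 36) × 6 = 432, which reproduces. Two observers × 3 × 2 h = 12 observer-hours a day. So 36 hours is 36/12 = 3 days if observer-hours are summed over roles, or 36/6 = 6 days if clock hours are meant. The article does not say which. The inflation below depends on f and not on the number of hours.

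**2. Variance.** Let each record cover T time units with discussion share p, and grant independent units within a record. The pooled share is (X_P + X_T)/(2T). The Z test takes the variance of X_P + X_T as 2Tp(1−p). Shared conversations give the two records a correlation of about f when p is small, so the true variance is about 2Tp(1−p)(1+f). The ratio is 1+f.

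**3. Error rate.** Actual alpha = 2 × [1 − Φ(1.96/√(1+f))]. Relative interval width = 1/√(1+f).

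| f | 1.96/√(1+f) | Actual alpha | Interval width, stated/correct |
|---|---|---|---|
| 0 | 1.96 | 5.0% | 1.00 |
| 0.10 | 1.87 | 6.2% | 0.95 |
| 0.25 | 1.75 | 8.0% | 0.89 |
| 0.50 | 1.60 | 11.0% | 0.82 |
| 0.75 | 1.48 | 13.8% | 0.76 |
| 1 | 1.39 | 16.6% | 0.71 |

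**4. Simulation check.** There were 20,000 null comparisons with 18 clock hours per role per period (assumed), minutes as units and 5% discussion time (assumed). With near-independent minutes the pooled test rejected 4.9% at f=0 and 16.6% at f=1. A pharmacist-only test rejected 5.0% and 5.2%. A separate simulation with independent minutes gave 10.6% at f=0.5, close to the formula.

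**5. Against serial dependence.** With discussion bouts averaging 3 minutes (assumed), the pooled test rejects 36.6% at f=0, 47.1% at f=0.5 and 52.2% at f=1. A pharmacist-only test still rejects about 37%. Double counting adds to this problem but is the smaller part of it.

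**6. Sessions as units.** Moving from minutes to sessions does not remove the duplication if each observer's session is one unit. On the observer-hour reading there are 18/2 = 9 simultaneous sessions per period, hence 18 observer-sessions. A t test of 18 against 18 observer-sessions, with within-pair correlation 0.25, 0.5, 0.75 and 1, rejects 7.8%, 11.0%, 15.1% and 18.3%. With 9 against 9 pair-session means it rejects 4.8–5.1% throughout.

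**7. Holm.** Under pooling, a first step of 0.05/12 = 0.0042 (12 comparisons assumed) has actual alpha of 0.010 at f=0.25, 0.019 at f=0.5 and 0.043 at f=1. Holm adjusts for the number of tests and cannot correct a wrong standard error inside one.

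**The case against.** The strongest objection is that the article never says the two records are pooled for this outcome. It speaks of both roles' distributions and plans one proportion for pharmacists alone. A reader might infer that every such conversation enters the Z test twice as a matter of fact; the text does not establish that. If the roles are tested separately, each test holds one copy of each conversation, and this mechanism leaves no fault in its standard error. Holm also remains valid for dependent tests, so the familywise rate is not inflated by testing both roles. What remains is a caution: two results drawn from the same conversations are not independent confirmation.

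Three further points stand:
- f is unknown. Only talk between the two people shadowed at that moment is duplicated, and the article does not say they work as a pair. The 17% figure is the upper end, not the expected value.
- The pharmacist proportion for tasks done with a technician comes from one role's record. A reader might extend the concern to it, but nothing there is entered twice.
- Serial dependence in the same Z test is the larger fault, and removing duplicates does not cure it.

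It can also be said that merging rules belong in an analysis plan that is not shown, and that Aim 3 is a pilot whose quantitative stage feeds further qualitative work. Both limit the consequences. They do not dispose of the point, because the article itself fixes the test, the interval method and the strata, and these do not suit simultaneous records pooled for a mutual outcome.

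**Conclusion.** The point holds conditionally. Simultaneous shadowing, a mutual-discussion outcome and a Z test with no role stratum are all in the text, and pooling is the most natural reading. Under pooling the estimate is unbiased, the variance is understated by about 1+f (at most a factor of 2), and a nominal 5% test runs at about 6% to 17% for f from 0.1 to 1. Those figures grant independent time units, which is generous to the plan; realistic bouts of conversation make the total error much larger for a different reason. With separate tests by role there is no double counting within a test. The documents do not support the stronger statement that P values are too small at every site because of this mechanism alone.

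**What to change.** For the staff-discussion outcome:
- State whether the pharmacist and technician records are pooled or tested by role, and whether the 36 hours per period are clock hours or summed observer-hours.
- If pooled, match the two time-stamped WOMBAT records of each simultaneous session, count a discussion between the two shadowed people once, and report it per clock hour. Using one role's record only is a simpler alternative.
- Replace the Z-test standard error with one that takes the simultaneous pair-session as the unit, using a t reference because there may be as few as 9 pair-sessions per period. State that clustering by only two staff per role per site remains.
- If tested by role, say that the two results share the same events and are not independent evidence.

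The pharmacist-only proportion needs no matching. The cost is analysis wording and a merge on time stamps, with no extra observation, staff or sites. The drawback is a wider interval for this outcome. The article says Aim 3 materials were still in development, so this can be settled before data collection.

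### The Z test for proportions does not fit shares of observed time: no unit of analysis is named, so P values and CIs depend on an arbitrary time unit and ignore clustering by session and person

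*Protocol article*

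**What the plan says.** In the Protocol article, Methods, Aim 3, Data Analysis, the outcome is a share of time: "we will calculate the proportion of total observed time in each task category by study period (before vs after implementation) for each pharmacy". The comparison is by Z "tests for proportions will be used to compare the extent of before and after implementation change in the proportion of total observed time", made "for each task category in each pharmacy site". Error control and intervals are fixed in the same place. The testing rule reads "A significance level of *P*<.05 will be used as well as the Holm approach to account for multiple comparisons", and results are to be reported "with 95% CIs based on the large sample normal approximation".

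The data behind these shares are described in the Aim 3 sections Time and Motion Study and Data Collection. The observation software records when each task starts and ends and allows simultaneous tasks. Sampling is by person and session: "In total, 2 pharmacists and 2 technicians will be observed at each pharmacy", in sessions of 2 hours, at most three a day, with one observer on a pharmacist while a second is on a technician. On volume: "The pharmacists and technicians will be observed for 36 hours both before and after implementation".

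The article does not say what n is in the Z test, and it mentions no allowance for correlation within session or person.

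**The concern.** A Z test for proportions takes its variance from p(1−p)/n, where n counts independent yes/no trials. A share of observed time is a ratio of durations and has no such n. If time units are used, whoever runs the analysis must choose hours, minutes or seconds, and the choice changes the P value without changing the data. Adjacent time units also belong to the same task, session and person, so they are not independent.

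These are the only inferential tests that the article specifies for the time and motion study. The Evaluation section says that the mixed methods approach, which starts from the quantitative data, will show which variables need further analysis. Misleading error bars could therefore steer the later work, towards noise if they are too narrow or away from real change if they are too wide. Holm allows for the number of tests. It takes each P value as valid and cannot repair a wrong standard error.

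**Working it through.** **Inputs from the article.** 36 hours observed before and 36 after in each pharmacy; 2-hour sessions; six pharmacies; two pharmacists and two technicians per pharmacy. The article's own total reproduces: (36 + 36) × 6 = 432 hours. It gives no variance, power or effective sample size for the Z test.

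**Assumptions, not in the article.** Two-sided tests; a task share of 10%; a between-session SD of that share of 5 percentage points (range 3 to 8); the 36 hours read as observer-hours, so 36 / 2 = 18 staff-sessions per period.

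**Step 1: dependence on the time unit.** Take a change from 10% to 12% in one pharmacy. The pooled share is 0.11, SE = sqrt(2 × 0.11 × 0.89 / n) and z = 0.02 / SE. The CI uses the unpooled SE.

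| n counted in | n per period | z | P | 95% CI, points |
|---|---|---|---|---|
| hours | 36 | 0.27 | .79 | −12.5 to 16.5 |
| minutes | 36 × 60 = 2,160 | 2.10 | .036 | 0.1 to 3.9 |
| seconds | 36 × 3,600 = 129,600 | 16.3 | <.001 | 1.8 to 2.2 |

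This step needs no assumption about variability. From minutes to seconds, z grows by sqrt(60) = 7.7 whatever the share.

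**Step 2: what independence would require.** At a 10% share, independent minutes imply a between-session SD of sqrt(0.09 / 120) = 2.7 points, and independent seconds imply sqrt(0.09 / 7,200) = 0.35 points. The sessions are deliberately spread over different weekday shifts to capture variability, so more spread than this is plausible. The article gives no figure for it.

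**Step 3: illustrative type I error with no true change.** The SE used by the test is sqrt(2 × 0.1 × 0.9 / n), which is 7.07, 0.91 and 0.12 points for hours, minutes and seconds. The SE from 18 independent sessions per period is sqrt(2 × SD² / 18), which is 1.00, 1.67 and 2.67 points for SDs of 3, 5 and 8. The error rate is 2 × (1 − Φ(1.96 × SE of test / SE from sessions)). For minutes and SD 5: 1.96 × 0.913 / 1.667 = 1.07, which gives 28%.

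| n counted in | SD 3 | SD 5 | SD 8 |
|---|---|---|---|
| hours | about 0% | about 0% | about 0% |
| minutes | 7% | 28% | 50% |
| seconds | 82% | 89% | 93% |

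If simultaneous pharmacist and technician sessions were fully correlated, 18 sessions would become 18 / 2 = 9 blocks, and the minute-level figures would be 21%, 45% and 64%.

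**Step 4: a check by a different route.** A simulation of on/off task bouts used a 10% share, mean bout 30 to 300 seconds, between-session SD 0 to 0.6 on the logit scale, 18 sessions per period and 1,000 runs per setting. Type I error was 79% to 96% in seconds and about 0% in hours. In minutes it was 4% with 30-second bouts and no session variation, and 13% to 62% in the other settings. A t test on session shares, 18 against 18, gave 3.5% to 5.5% on the same data. That simulation took sessions as independent and did not model clustering by the four staff.

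**The case against.** The strongest reply is that the article names no time unit. A reader might infer that minutes or seconds will be treated as independent trials, but that is nowhere stated. The CI wording alone would also permit a standard error estimated across sessions, and an article may leave such detail to a fuller document. The part about the unit stands. It does not rescue the plan, because the article itself fixes the test, and a test for proportions in its standard form does not use a between-session variance. If n were the number of tasks, the test would address a proportion of tasks and no longer the stated proportion of time.

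A reader might also infer that type I error is far above 5%. The documents do not support that as a fact. The share and SD are assumed, hours as the unit would make the test very conservative, and minutes can be near nominal when bouts are short and sessions do not vary.

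The count of 18 sessions is an assumption too. The 36 hours could be clock hours for each of the two observers. Then n and the number of sessions both double and the error rates in step 3 do not change, although z in step 1 rises by sqrt(2), for example from 2.10 to 2.97 in minutes.

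It is tempting to say that a pharmacist–technician discussion seen by both observers is counted twice. It is not: the outcome is time spent by each role, and a shared discussion uses observed time of both. The overlap is a correlation to be allowed for.

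Finally, aim 3 is a pilot, the point estimates are unaffected, and the article ties no primary hypothesis or power claim to these tests. That limits the consequences. It does not make the stated intervals valid.

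**Conclusion.** The point holds as a mismatch between the named test and the data. Followed as written, the Z tests and normal-approximation CIs give results that depend on an unnamed unit and ignore correlation within session and person. The dependence on the unit is arithmetic and rests only on the 36 hours per period and the example shares. The type I error figures are illustrations under the assumed share and SD, and they show that the error can run either way. The documents do not show which unit will be used or how large the distortion will be. Because the article states the test and the interval method outright, this is a wrong choice in the text and more than an omitted detail.

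**What to change.** Replace the Z tests and normal-approximation CIs in the Aim 3 Data Analysis section with an analysis whose unit is the 2-hour observation session:

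- Compute each session's share of time per task category.
- Keep the before–after comparison within each pharmacy, using session shares with a small-sample t-based interval or a block bootstrap that resamples simultaneous pharmacist and technician sessions together.
- Label the per-pharmacy results descriptive or exploratory. With four staff per site, variation between people can hardly be estimated there, and session-level methods do not fully remove it.
- If an overall estimate is wanted, add a mixed model across pharmacies with random effects for pharmacy, staff member and shared session, and say that this is a pooled estimand, different from the per-pharmacy comparison.
- Keep each person's time in a shared discussion and model the correlation. Counting the discussion once, with both people's time still in the denominator, would understate the share.

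The cost is a change of wording with no new data. Intervals will be wider and fewer results will be nominally significant. The article dates the start of aim 3 to January 2026 and describes its materials as still in development, so the change fits best before those data are analysed.

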### Pharmacy-Reported Data

We anticipate that MedSafeMap will support pharmacists’ and technicians’ ability to embed CCM and other clinical services into their workflow, which will improve the quality of patient care, ideally, without increasing workload. To assess perceived changes in service provision, pharmacists and technicians will be administered a validated subjective workload survey [61]. Moreover, the number and type of documented medication-related problems during CCM services [62] that are identified and resolved for 6 months before and 12 months following MedSafeMap implementation will be collected. Pre-post comparisons of services provided and medication-related problems that they averted will be conducted.

### Pharmacist and Technician Evaluation

We also want to gain a more in-depth understanding of how MedSafeMap changed attitudes, behaviors, and performance. It is expected that pharmacists and technicians will feel more resilient after the implementation of MedSafeMap, that is, they will feel more “capable, facilitated, and supported by the organization to utilize resources to continually adapt and flourish at work, even if/when faced with challenging circumstances” [63]. This construct will be represented through the Employee Resilience Scale [63], a measure of behavioral elements, such as learning orientation, proactive posture, positive outlook, network leveraging, and adaptive capacity.

Pharmacists and technicians also are likely to eventually feel a greater sense of shared responsibility and teamwork, which would create an environment that enhances the medication safety of their patients. This construct will be represented through the National Aeronautics and Space Administration (NASA)–developed Cockpit Management Attitudes Questionnaire [64,65], comprising 3 scales, namely communication and coordination, command responsibility, and recognition of stressor effects, which have application for the pharmacy work system.

Because we are working with a small number of pharmacists and technicians and we want to conduct an in-depth exploration of pharmacy staff attitudes and behaviors, we will adapt the Employee Resilience and Cockpit Management Attitudes Questionnaire items into an interview guide that will include semistructured probes. In addition, 8 months following MedSafeMap’s implementation, interviews will be conducted using a retrospective pre- and posttest design approach [66,67] by asking, “Compared to before MedSafeMap was implemented...” This approach is appropriate because it is pragmatic and less time consuming, eliminates the impact of response-shift bias [66], and has been used successfully in pharmacy studies [68,69]. Questions will prompt insights into the impact of MedSafeMap on pharmacist and technician resilience, teamwork, and shared responsibility. Interview data will be subjected to the same rigorous qualitative data analysis techniques described in aim 1.

### Outcomes

Study outcomes are targeted to help populations of medication safety researchers and organizational leaders responsible for implementing proven practices. A summary of the anticipated outcomes can be found in Textbox 4.

Anticipated outcomes.
**Aim 1**
Resilience narratives and functional resilience analysis method models that are context rich and context dependentPotential to uncover anticipated relationships between variables that can be tested in the subsequent aims to inform the development of the Medication Safety Map (MedSafeMap)
**Aim 2**
Components of MedSafeMap that support chronic care management in community pharmaciesMedSafeMap components that may include designs that realign currently existing tasks, coordinate tasks with different pharmacy staff members, or incorporate new practicesMedSafeMap components that may include tools to facilitate pharmacist and patient and pharmacist and prescriber collaboration or to provide cognitive support for pharmacists and technicians to anticipate crises or other problems
